#### Power analysis

For aim 1 (effectiveness), our final sample will include 25 students per school (*n* = 20 schools; 500 students total). With 50% of students in the intervention group and 50% in the control group, using effects sizes, variance, and cluster effects based on prior research [27], calculations indicate 447 students are needed to achieve a power of 0.80 to detect group differences in BMI z-score. We will recruit 500 students to account for a 5% loss to follow up.

Given that we have made additional modifications to the school-to-school mentoring strategy, we consider aim 2 (implementation) to be a pilot cluster randomized controlled trial. Best practices suggest that pilot studies focus on logistics and refinement of implementation protocols, which we will iteratively address through this study [68]. Still, based on our expected recruitment of 20 schools with 8–10-person implementation teams, using a beta of 0.8, a type I error rate of 0.05, and an intraclass correlation coefficient of 0.015–0.030, we are powered to detect a small-to moderate mean difference of 0.25—0.27 points on a 5-point scale (effect size of d = 0.45).

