**Methods:**

Students in 4th through 9th grade (*n* = 500) at public schools (*n* = 20) across East and Central Texas will be randomized at the school level to determine the effectiveness of HSRC (vs. waitlist control condition) on BMI z-score (primary outcome), physical activity measured via accelerometer, and skin carotenoids (i.e., fruit and vegetable intake; secondary outcomes). Assessments will occur at the start and end of one school year. Program implementers (*n* = 200) at schools will be randomized to assess the impact of the school-to-school mentoring strategy (vs. standard implementation) on HSRC’s acceptability, appropriateness, and feasibility (co-primary outcomes). Assessments will occur at the start, middle, and end of one school year. The assessment at the end of the school year will also include a concurrent mixed-methods approach (QUAL + QUAN), guided by the Consolidated Framework for Implementation Research (CFIR), to evaluate the school-to-school mentoring strategy. For quantitative outcomes, a generalized linear model framework will be used to evaluate HSRC and the school-to-school mentoring strategy.

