### Study design

This study uses a hybrid type 2 implementation-effectiveness, cluster dual randomized controlled trial (DRCT; Fig. 1). DRCTs include two randomized controlled trials within the same study: one testing the intervention (i.e., HSRC) and one testing an implementation strategy [37–39]. DRCTs allow for rigorous testing of both the effectiveness of an intervention and the impact of an implementation strategy on outcomes, accelerating the translation of interventions into practice [37–39]. For the effectiveness aim (Aim 1), we will compare outcomes in ten Texas schools that receive HSRC with ten waitlist control schools (Fig. 1 in gray). For the implementation aim (Aim 2), ten schools will be randomized to receive a school-to-school mentoring program, and ten will receive standard implementation of the program (Fig. 1 in blue).

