#### HSRC implementer eligibility and recruitment

Extension agents will build an implementation team of 5–10 people to support the HSRC programs at their school (e.g., approval, planning, and/or facilitation of HSRC). The implementation team may include school administrators (e.g., principal, vice-principal, superintendent), classroom teachers, physical activity staff (e.g., physical education teachers), nutrition staff (e.g., school nutrition directors), parent-teacher organization members, volunteers, other Extension agents, student implementers, or any other role that supports HSRC programs (e.g., school health advisory council members). Once Extension agents have built their teams, they will provide the names and contact information to the research staff. The research staff will send study information and an enrollment invitation to all implementation team members, including the Extension agent who formed the team, via email. Adult implementers must be at least 18 years of age and able to speak, read, and write in English to consent. Youth implementers will need a caregiver at least 18 years old to sign a consent form, and they must be able to speak, read, and write in English to participate.

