This study further advances implementation science through its use of a hybrid type 2, cluster DRCT, which allows for simultaneous evaluation of both the effectiveness of the intervention (i.e., HSRC) and the impact of the implementation strategy (i.e., school-to-school mentoring) on outcomes [37–39]. By randomizing schools to HSRC or waitlist control, and to different implementation conditions, this study provides a unique opportunity to link improvements in HSRC’s implementation to changes in students’ health behaviors and outcomes. Additionally, the use of randomization to answer both implementation and effectiveness questions reduces selection bias, balances measured and unmeasured confounders across schools, and enhances the validity of causal inferences within both trials [73]. Furthermore, as both aims have adequate statistical power to detect small-to-moderate effects, our design makes efficient use of resources to conduct two randomized trials answering important questions that can help to close the research-to-practice gap.

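### The Aim 2 power statement (80% for d = 0.45) is not delivered across the team sizes the protocol itself gives

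*Protocol article*

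**What the plan says.** The Power analysis section makes the Aim 2 calculation "based on our expected recruitment of 20 schools with 8–10-person implementation teams, using a beta of 0.8, a type I error rate of 0.05". The ICC assumed is 0.015 to 0.030. It concludes that a difference of 0.25 to 0.27 points on the 5-point scale, d = 0.45, can be detected.

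Team size appears in two other places:
- HSRC implementer eligibility and recruitment: "Extension agents will build an implementation team of 5–10 people to support the HSRC programs at their school".
- Abstract, Methods: "Program implementers (*n* = 200) at schools will be randomized". Over 20 schools, 200 is ten per school.

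Study design gives the allocation: "ten schools will be randomized to receive a school-to-school mentoring program, and ten will receive standard implementation of the program".

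On the standing of Aim 2, the Power analysis says "we consider aim 2 (implementation) to be a pilot cluster randomized controlled trial", while the Discussion says "both aims have adequate statistical power to detect small-to-moderate effects".

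**The concern.** Three sections imply three sample sizes for one comparison: 200 implementers (Abstract), 160 to 200 (Power analysis, 20 × 8 to 20 × 10) and 100 to 200 (recruitment, 20 × 5 to 20 × 10). One effect size, d = 0.45, is printed for all of them. If it fits only the upper end, the power is overstated for the team sizes that the recruitment section permits.

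Two further points bear on the same sentence. Aim 1 is inflated for 5% loss to follow-up, but no allowance is stated for Aim 2. Yet its participants are enrolled by e-mail invitation and its analysis uses both a baseline and a post-test survey. And a beta of 0.8, taken literally, is a power of 20%.

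At stake is how a null mentoring result is read. A reader who trusts the claim of adequate power would count it as fair evidence that a difference of d = 0.45 is absent. With fewer surveys than the calculation needs, that reading is weaker than it looks.

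**Working it through.** **Inputs.** Ten schools per arm (Study design). ICC 0.015 and 0.030, d = 0.45, type I error 0.05 (Power analysis). Assumptions: two-sided test (sidedness is not stated), the beta of 0.8 read as power 0.80, equal numbers per school, no baseline adjustment. *m* is the number of completed surveys per school.

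**Formulas.** Design effect DE = 1 + (*m* − 1) × ICC. Effective number per arm n = 10*m*/DE. Standard error in SD units SE = √(2/n). Detectable d = (1.960 + 0.842) × SE. Power for d = 0.45 is Φ(0.45/SE − 1.960).

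**Reproducing the stated figure, *m* = 10.**
- ICC 0.015: DE = 1.135, n = 100/1.135 = 88.1, SE = 0.151, d = 0.42, power 85%.
- ICC 0.030: DE = 1.27, n = 100/1.27 = 78.7, SE = 0.159, d = 0.45, power 81%.

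The article gives no SD. With SD 0.60 (0.27/0.45), these d values are 0.25 and 0.27 points, the printed range. This is not the only match: *m* = 9 gives d = 0.442 and 0.465, which with an SD of 0.57 is also 0.25 and 0.27 points. So the SD behind the points values cannot be recovered from the article.

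**Over the documented team sizes** (each pair is ICC 0.015 / 0.030):

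| Surveys per school | DE | Detectable d | Power at d = 0.45, normal | Power at d = 0.45, t on 18 df |
|---|---|---|---|---|
| 10 | 1.135 / 1.27 | 0.42 / 0.45 | 85% / 81% | 81% / 76% |
| 9 | 1.12 / 1.24 | 0.44 / 0.47 | 81% / 77% | 77% / 73% |
| 8 | 1.105 / 1.21 | 0.47 / 0.49 | 77% / 74% | 73% / 69% |
| 7.5 | 1.0975 / 1.195 | 0.48 / 0.50 | 75% / 71% | 70% / 67% |
| 5 | 1.06 / 1.12 | 0.58 / 0.59 | 59% / 57% | 54% / 52% |

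Detectable d is by normal approximation. The last column uses the noncentral t with 20 − 2 = 18 degrees of freedom, which reflects the small number of schools.

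**Surveys needed.** Setting detectable d to 0.45 and solving, *m* = (1 − ICC)/(10 × 0.45²/(2 × 2.802²) − ICC). The first term of the denominator is 2.025/15.70 = 0.1290. So *m* = 0.985/0.1140 = 8.6 at ICC 0.015 and 0.970/0.0990 = 9.8 at ICC 0.030.

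**Unreturned surveys.** Starting from ten per school, a 5% loss (the Aim 1 allowance, used only as an illustration) leaves 9.5. Power is then 83% at ICC 0.015 and 79% at ICC 0.030.

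**Baseline adjustment.** If baseline and final scores correlate at r, the variance falls by about 1 − r². Reaching 80% needs r² = 1 − (0.45/d)². No r is given, so these are thresholds and not estimates.
- *m* = 8: 1 − (0.45/0.4656)² gives r = 0.26; 1 − (0.45/0.4873)² gives r = 0.38.
- *m* = 5: 1 − (0.45/0.577)² gives r = 0.63; 1 − (0.45/0.593)² gives r = 0.65.

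With an assumed r = 0.5 (variance factor 0.75), power is 88%/85% at eight and 71%/69% at five.

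**The case against.** The strongest reply is the planned analysis. Aim 2 follows the Aim 1 model, with the baseline score as a covariate, and a modest correlation of 0.26 to 0.38 would restore 80% at eight per school. This stands as a real possibility. But the Power analysis claims no such gain, and at five per school the correlation would have to be about 0.63 to 0.65.

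Second, 5 to 10 may be a permitted range and 8 to 10 an expectation within it, so the two need not contradict each other. That is fair. It does not rescue the figure, because eight lies inside the statement's own range and still falls short without adjustment.

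Third, multiple imputation is planned, so a missing survey does not automatically remove a person. True, but imputation does not restore all the lost information.

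Fourth, Aim 2 is called a pilot, and the Discussion looks ahead to a later, fully powered trial. This lowers the consequence. It does not square with the Discussion's claim of adequate power for both aims.

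Stronger readings a reader might infer, which the documents do not support:
- That the statement holds only with ten surveys at every school. Nine per school at ICC 0.015 gives 81%, and the requirement is on the mean.
- That power is 52 to 59%. That span mixes two methods and puts all 20 schools at the minimum team size.
- That the three outcomes ("acceptability, appropriateness, and feasibility (co-primary outcomes") inflate the type I error or cut the power. Either depends on a success rule that may sit in the analysis plan, which is not shown. It is a separate matter.

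**Conclusion.** The point holds in a limited form. The printed d = 0.45 at 80% power fits the upper end of the team sizes and not the range. Unadjusted and by normal approximation, the shortfall at eight per school is about 3 points of power at ICC 0.015 and 6 to 7 at ICC 0.030. At the 7.5 midpoint it is about 5 and 9 points. With five at every school, an extreme case, it is about 21 and 23 points. On t with 18 df, even ten per school gives only 76% at ICC 0.030.

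These sizes rest on a two-sided test, equal school sizes and no gain from the baseline covariate. Whether the calculation behind the article included such a gain cannot be known from the text. What needs no assumption is that the team sizes in three sections differ, that beta is mislabelled, and that the pilot label and the claim of adequate power do not sit together. Severity: should be fixed.

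**What to change.** 1. Reconcile team size across the Abstract, the recruitment section and the Power analysis, and state the expected number of completed surveys per school after non-response.
2. Restate the detectable d over the planned range using one method. By normal approximation at ICC 0.030 it is about 0.45, 0.49 and 0.59 for 10, 8 and 5 completed surveys per school.
3. Give the SD that converts d to points, and any baseline correlation relied on.
4. Replace the beta of 0.8 with a power of 0.80.
5. In the Discussion, limit the adequate-power claim for Aim 2 so that it matches the pilot status.

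This costs wording only, at the price of a less favourable detectable difference unless a baseline correlation is justified. No school or implementer needs to be added.

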## Discussion

Overall, we will use a hybrid type 2 implementation-effectiveness cluster DRCT to evaluate the effectiveness of the HSRC initiative on BMI z-scores and the impact of the school-to-school mentoring strategy on implementation outcomes. The HSRC initiative bundles multiple research-based physical activity and healthy eating programs to be delivered by one of the largest Extension networks in the United States [24–27]. Given the high rates of cardiovascular and other chronic disease risk factors in Texas – about 10% of students have three risk factors (e.g., metabolic syndrome) – scalable school- and community-based approaches are needed to address them [27]. Texas A&M AgriLife Extension has 250 offices, 900 Extension agents (i.e., health educators), and a network of about 100,000 volunteers that can provide schools with the adequate support to deliver HSRC programs [69]. If the research-based programs that are included within HSRC can improve physical activity, healthy eating, and weight outcomes as well as, or better than, current school-based approaches, AgriLife Extension will be well-positioned to address cardiovascular and other chronic disease risk factors among youth across Texas.

Unlike one-size-fits-all implementation strategies [70], we iteratively developed and refined our school-to-school mentoring strategy in partnership with Extension agents to address their real-world barriers to implementation. Iterative development that follows structured processes – such as the multiphase optimizations strategy’s (MOST) preparation, optimization, and evaluation phased approach – have been shown to drive continuous improvement and foster adaptability of implementation strategies to various contexts [71, 72]. Previously, as part of our formative research (i.e., preparation), we surveyed and interviewed extension agents that were already delivering HSRC [26]. Through this work, we found that tangible resources enabled the implementation of HSRC, and that stakeholder buy-in, implementation climate, and learning climate were related to the acceptability, appropriateness, and feasibility of HSRC [26]. These findings ultimately led to the development of three implementation strategies. Subsequently, we conducted a cluster randomized factorial trial to optimize our implementation approach by evaluating the independent and combined (i.e., synergistic, antagonistic) impact of the three implementation strategies (incentives, contests, mentoring) on HSRC’s delivery [24, 72]. Preliminary findings from that study indicated that school-to-school mentoring (alone) was the best method for facilitating the implementation of HSRC, but that it still needed additional refinement. Building on these insights, the current study evaluates this refined strategy using a more rigorous, randomized, waitlist-controlled design. Results from this study can inform additional refinements, if needed, and better identify ways in which the school-to-school mentoring strategy supports agents and school stakeholders in the delivery of HSRC.

This study further advances implementation science through its use of a hybrid type 2, cluster DRCT, which allows for simultaneous evaluation of both the effectiveness of the intervention (i.e., HSRC) and the impact of the implementation strategy (i.e., school-to-school mentoring) on outcomes [37–39]. By randomizing schools to HSRC or waitlist control, and to different implementation conditions, this study provides a unique opportunity to link improvements in HSRC’s implementation to changes in students’ health behaviors and outcomes. Additionally, the use of randomization to answer both implementation and effectiveness questions reduces selection bias, balances measured and unmeasured confounders across schools, and enhances the validity of causal inferences within both trials [73]. Furthermore, as both aims have adequate statistical power to detect small-to-moderate effects, our design makes efficient use of resources to conduct two randomized trials answering important questions that can help to close the research-to-practice gap.

A recent review identified three previous trials that used a DRCT design, none of which have published results, and none conducted in community-based settings [37–39]. Consequently, our study presents the first use of the DRCT within schools and within an Extension network. The DRCT was chosen not only for its scientific rigor, but also to help with some of the common challenges that occur when conducting research in communities. For example, control groups in effectiveness trials often receive no intervention or subpar implementation of the intervention (e.g., less attention) after serving as a control (i.e., waitlist control). In our study the waitlist control group will be randomized to the enhanced implementation strategy or standard implementation helping to ensure that schools in the waitlist control condition receive the same level of implementation support as schools that were randomized to receive the intervention immediately. Similarly, a delay in time to receiving an intervention (i.e., waiting one year) has the potential to affect implementation of that intervention. The DRCT balances both implementation strategy groups (enhanced vs standard) on whether they receive the intervention immediately or must wait one year, balancing this potential confounder across condition reduces this potential bias better than other types of designs often used in the community setting (e.g., step-wedge design). Consequently, findings from our trial will help to identify potential benefits and barriers to using the DRCT design in community settings, which can inform future research efforts.

Our mixed-methods approach to evaluating the school-to-school mentoring strategy strengthens this study’s contributions to the literature on implementation strategies. A mixed-methods approach will provide more comprehensive data than either qualitative or quantitative approaches alone, and it enables a greater understanding of multiple implementer experiences [65]. In this case, our mixed methods approach will help us to better understand the potential mechanisms by which the school-to-school mentoring program affects implementation outcomes, it provides insight into how and why the strategy works, or where challenges persist, and it will inform how different roles within the HSRC implementation team differentially experience the strategy. This level of detail in understanding how the school-to-school mentoring strategy works will help us to tailor the strategy to distinct roles in the future. Furthermore, our mixed methods approach enables us to contextualize quantitative results, identify necessary adaptations, and determine whether the strategy is feasible and sustainable across diverse contexts [65]. For example, components of the enhanced implementation strategy, such as the newsletter, text messages, and virtual meetings with implementers, may be transferable to other community-based delivery settings where physical activity and nutrition programs are delivered (e.g., recreation centers, churches, workplaces). If HSRC is effective at improving health behaviors and outcomes, and the school-to-school mentoring strategy improves implementation as we hypothesize, HSRC and the school-to-school mentoring strategy will be ready for scaleup statewide and/or adapted for use with other Extension networks across the United States. Consequently, the results from this study will help develop a foundation that can be utilized to prepare a fully powered, hybrid type 3 implementation-effectiveness or a dissemination trial [71].

## Conclusion

Using a hybrid type 2 implementation-effectiveness framework, this study employs a DRCT design to evaluate both the HSRC initiative and a refined implementation strategy (i.e., school-to-school mentoring). The first embedded trial examines the effectiveness of the HSRC initiative on student obesity, physical activity levels, and skin carotenoid levels. The second embedded trial examines whether the school-to-school mentoring strategy enhances the delivery of HSRC. Findings from the qualitative and quantitative data collected during this study will inform future school-based intervention design, provide practical guidance for implementing school- and research-based health programs, and lay the groundwork for expanding HSRC to schools nationwide.

## Data Availability

No datasets were generated or analysed during the current study.

## Abbreviations

AIM: Acceptability of Intervention Measure
BMI: Body Mass Index
CFIR: Consolidated Framework for Implementation Research
DRCT: Dual Randomized Control Trial
FIM: Feasibility of Intervention Measure
HSRC: Healthy School Recognized Campus
IAM: Intervention Appropriateness Measure
ICC: Intraclass Correlation Coefficient
PACER: Progressive Aerobic Cardiovascular Endurance Run
SI: Standard Implementation
TEKS: Texas Essential Knowledge and Skills
WC: Waitlist Control
